#### Exploratory outcomes

Data will be collected prospectively via electronic health records. These measures will be compared to a historical cohort using the existing UCFC database, which has been previously approved by IRB protocol # 2216195–2 at UC Davis, and IRB protocol # 24–6179 at UCLA.

Exploratory clinical endpoints will include (1) length of hospitalization (days), (2) time to initiation of feeds from final abdominal closure (days), (3) time to full feeds (100 mL/kg/day or PO ad libitum whichever comes first) from final abdominal closure (hours), (4) duration of parenteral nutrition (days), (5) days of any human milk which includes parent’s own milk and/or donor breast milk during hospitalization, (6) any direct breastfeeding during hospitalization, (7) any direct breastfeeding at discharge (defined as 48 h prior to hospital discharge) (8) any use of parent’s own milk at discharge (defined as 48 h prior to hospital discharge), (9) growth parameters (delta-z-scores for weight and length (discharge–admission measurements).

The length of hospitalization refers to the total number of days spent in the hospital during the initial birth hospitalization. Generally, this will be days in the neonatal intensive care unit (NICU) but can also be days in the pediatric intensive care unit (PICU) or pediatric wards. This will be measured via midnight census data from electronic health records (EHR). Feeding progression covers the initiation of feeds, defined as time to first feed and time to full feeds, both in days. The duration of PN is measured as the number of days of PN. Rates of direct breastfeeding are defined as direct breastfeeding 48 h before discharge. Outcomes of adverse events include rates of necrotizing enterocolitis (> Stage II), sepsis, abdominal compartment syndrome, additional abdominal surgeries (excluding primary closure), and mortality. Medical errors and adverse events will be obtained via solicited reports and review of EHR data.

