### Data collection and management

#### Plans for assessment and collection of outcomes

Feasibility objectives will be assessed by tracking the number of neonates approached, enrollment rates, milestone achievement (such as initiation of feeds within 48 h of abdominal closure), and withdrawal rates. Data for the intervention group will be collected prospectively from the electronic health record (EHR) prenatally and through the initial hospital discharge.

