#### Methods for additional analyses, including comparisons to historical controls

We recognize that accounting for specific confounders, such as site, gestational age, birth weight, sex, and race/ethnicity, is important. If feasible, we may consider performing sub-analyses or accounting for these variables in specific models. However, we recognize that our sample size is small and our results most likely will not be generalizable.

For comparisons to historical controls on the study variables described earlier, we anticipate being able to obtain patient-level data from the historical controls, permitting us to use linear and logistic regression to estimate adjusted mean differences or adjusted odds ratios, respectively, with 95% confidence intervals for the current vs. historical control comparisons, adjusting for study site. Continuous outcomes may be log-transformed to improve the validity of the normality assumption, with the Van Elteren test (stratified Wilcoxon Mann–Whitney) used as a backup if parametric tests are not appropriate. If patient-level data from the historical controls is not available but means and/or proportions are available, we will instead estimate stratified means and/or proportions for the current cohort with 95% confidence intervals, permitting comparisons to the historical means and proportions.

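### Length of stay and PN days are compared with historical controls as complete values, although death and discharge on PN, and possibly transfer, cut them short

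*Protocol article*

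**What the plan says.** All references are to the protocol article.

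- **Length of stay** (Exploratory outcomes): "The length of hospitalization refers to the total number of days spent in the hospital during the initial birth hospitalization". NICU, PICU and ward days all count. The named source is the census: "This will be measured via midnight census data from electronic health records (EHR".
- **PN duration** (same section): "The duration of PN is measured as the number of days of PN". No end event is attached to the count.
- **Data window** (Plans for assessment and collection of outcomes): records for the intervention group are collected "prenatally and through the initial hospital discharge".
- **Comparator** (Exploratory outcomes): "These measures will be compared to a historical cohort using the existing UCFC database".
- **Method** (Methods for additional analyses): with patient-level historical data, the investigators will use "linear and logistic regression to estimate adjusted mean differences" or odds ratios, adjusted for site and with 95% confidence intervals. Log transformation is an option for continuous outcomes, and the Van Elteren test is the backup. Without patient-level data, only means or proportions are set beside each other.
- **Population** (section on non-adherence and missing data): every enrolled infant is analysed, whether or not the protocol was followed. The rule for unknown status covers the feasibility outcomes only.
- **Mortality** (Exploratory outcomes): listed among the adverse events and not linked to either duration.

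**The concern.** A day count that ends at discharge measures the full course only for an infant who goes home alive and off PN. The other dispositions do not go missing. They contribute a number, and the named methods accept it as a finished duration.

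- **Death.** The infant has few hospital days and few PN days, so the worst outcome takes a value at the good end of both scales.
- **Discharge on PN.** The stay is a true stay, but PN given at home is not counted.
- **Transfer to another hospital.** If the census count stops when the infant leaves the site, both durations are cut.

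Shorter PN dependency and shorter hospitalization are the benefits stressed in the study rationale, and the plan commits to adjusted differences with confidence intervals on them. If the two cohorts differ in how often these events occur, or in how the historical database recorded them, part of the reported difference reflects disposition and not feeding.

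**Working it through.** **Plan's own figure.** There is none on this point. The only precision figures, in the Sample size section, are error margins for proportions and do not bear on the durations. They do reproduce: 1.96 × √(0.25/40) = 15.5 points and 1.96 × √(0.25/20) = 21.9 points, against stated limits of 16 and 22.

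**Inputs from the document.** Enrolment is 20 (Sample size). Average PN duration is 25 days (Introduction, section on management challenges). Rates of death, transfer or discharge on PN, and the historical recording rules, are not given. Every event day below is an assumption.

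**1. Early death, arithmetic mean.** If the other 19 infants average 25 PN days and one dies with *t* recorded days, the mean falls by (25 − *t*)/20.
- *t* = 5: (25 − 5)/20 = 1.0 day
- *t* = 3: 22/20 = 1.1 days
- *t* = 14: 11/20 = 0.55 day
- Two such deaths double these values, to between 1.1 and 2.2 days over *t* = 14 to 3.

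**2. Log transformation.** Short values gain leverage. Replacing one value of 25 by 5 among 20 multiplies the geometric mean by exp(−ln 5/20) = 0.923. That is a fall of 7.7%, or about 1.9 days on a geometric mean of 25.

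**3. Van Elteren test.** Without a rule for deaths, the same infant receives one of the shortest, and so most favourable, ranks in its site stratum.

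**4. Truncation at discharge on PN or at transfer.** If *k* of 20 infants are recorded at *t* days when the full course would be *T*, the mean is understated by *k*(*T* − *t*)/20.
- *k* = 1, *t* from 5 to 20, *T* from 40 to 90: smallest (40 − 20)/20 = 1.0 day, largest (90 − 5)/20 = 4.25 days
- *k* = 2: 2.0 to 8.5 days

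A truncated count need not be a low one. An infant sent home on PN at day 60 who needs 120 days understates the mean by (120 − 60)/20 = 3.0 days. Yet compared with a 25-day infant in the same place, the recorded 60 raises the mean by (60 − 25)/20 = 1.75 days.

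**5. Effect on the comparison.** Let *f* be the fraction of infants affected and *L* the mean days lost per affected infant. The bias in current minus historical is −*f*(current) × *L*(current) + *f*(historical) × *L*(historical). With *L* = 20 in both cohorts and 5% affected in the current one (1 of 20):
- historical 0%: −1.0 day, which looks like benefit
- historical 5%: −1.0 + 1.0 = 0
- historical 10%: −1.0 + 2.0 = +1.0 day, which looks like harm

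The sign depends on the two cohorts' event rates and recording, which the document does not give.

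**The case against.** The strongest objection is that this is an absent rule and not an error. A journal article condenses the full protocol, and handling of death or censoring commonly sits in an analysis plan that is not shown. That limits the weight of the point but does not remove it. The article fixes the data window, the population and the methods, and in combination these treat an early death as a short, complete course.

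A reader might go further and infer that both durations stop at the site's own discharge, and that death, transfer and discharge on PN all give short values favouring early feeding. The document does not support that.
- It speaks of the initial birth hospitalization. That the count ends at transfer is an inference from the census source, and days at a receiving hospital are neither included nor excluded. The wide referral area under Study setting describes referral in, not transfer out.
- Discharge on PN leaves length of stay correct, and the PN count can be truncated and still high (step 4).
- If both cohorts are recorded alike and have similar event rates, the distortion largely cancels (step 5).

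The retention section says hospitalization results will still be gathered where possible for infants who leave the protocol. That helps against missing data but does not say how a death or a PN course continuing at home enters the analysis.

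It is also tempting to set the shifts beside the meta-regression figures in the Introduction (2.1 PN days and 1.9 hospital days per day of feeding delay). Those figures are for one day's delay. If feeds start 5 to 10 days earlier (assumed), the same association implies 10.5 to 21 PN days, so one or two affected infants would not match the effect hoped for.

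Finally, the outcomes are exploratory, efficacy testing is disclaimed, mortality is reported separately, and no feasibility objective is touched. All of that stands.

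**Conclusion.** The point holds in a limited form. As planned, an early death counts as a short stay with few PN days, and PN after discharge is lost. If the census ends at transfer, which the text leaves open, both durations are truncated for that infant too. None of the named methods corrects this, and log transformation increases the pull of a short value.

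The size is illustrative only: about 1 day of mean PN per early death among 20 infants, assuming 5 recorded days against the 25-day average. It is 1.0 to 4.25 days per infant truncated at discharge or transfer, under the ranges assumed above. These are shifts in one cohort's mean. Bias in the comparison requires that event rates or recording differ between cohorts, and it can run either way. The point is a low-cost improvement to exploratory analyses and does not threaten the feasibility aims.

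**What to change.** 1. Extract discharge disposition for both cohorts (home off PN, home on PN, transferred, died) and report the counts by cohort beside the two durations.
2. State whether days at a receiving hospital belong to the birth hospitalization, and apply the same answer to both cohorts.
3. For the two durations, use the site-stratified Van Elteren test that is already named, with deaths given the worst rank.
4. Add a supporting time-to-event summary with end events of discharged home alive and off PN. Censor stay at transfer, and PN at transfer or at discharge on PN. Treat death as a competing event. Use identical rules in both cohorts. Infants sent home on PN probably need it for longer than those still in hospital, so this censoring is likely to be informative. That is a reason to keep the summary supportive and to show the counts.
5. If only historical means are available, these rules cannot be applied to the historical side. Report the current cohort's dispositions and say that the historical ones are unknown.

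The cost is one extra field and a few sentences of analysis text, best settled before the historical data are extracted. A rank or time-to-event result then stands beside the simple mean difference, and the disposition field must exist in the historical database, which the document does not confirm.

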**Methods:**

This two-site single-arm feasibility trial aims to enroll neonates with presumed simple gastroschisis over 30 months. The intervention has two main components: Replogle suction tube removal within 24 h of abdominal closure and starting small-volume human milk feeds within 48 h of abdominal closure. Feeding volume will be advanced as tolerated, following the University of California Fetal Consortium pathway, which is standard care. Feasibility outcomes include enrollment rate, protocol adherence, fidelity, and withdrawal rate. Exploratory outcomes include hospitalization length, time to full feeds, duration of parenteral nutrition, use of human milk, breastfeeding rates, and anthropometric measurements. Safety measures involve monitoring for feeding-related complications, infections, and unexpected surgical interventions.

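### The NEC safety outcome is written as above Stage II, so Stage II cases are left out of the reported rate; the surgery item also needs its wording reconciled

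*Protocol article*

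**What the plan says.** The adverse event outcomes are in the Protocol article, Exploratory outcomes: "Outcomes of adverse events include rates of necrotizing enterocolitis (> Stage II), sepsis, abdominal compartment syndrome". From the stage cut-off to its end, the list reads "Stage II), sepsis, abdominal compartment syndrome, additional abdominal surgeries (excluding primary closure), and mortality". The same section adds that "Medical errors and adverse events will be obtained via solicited reports and review of EHR data". Its opening paragraph says that the measures will be compared with a historical cohort from the consortium database.

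The abstract (Methods) describes the aim in different words: "Safety measures involve monitoring for feeding-related complications, infections, and unexpected surgical interventions". The Objectives list safety among the components of feasibility.

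On closure, Exploratory outcomes starts the feeding clocks at 'final' closure, for example "time to initiation of feeds from final abdominal closure (days". The surgery item refers instead to 'primary' closure. The article defines neither term.

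**The concern.** A strict greater-than sign puts Stage II itself outside the rate. The intervention is earlier feeding and the abstract singles out feeding-related complications for monitoring, so the NEC rate is one that readers will look at first. A rate that omits one stage of the disease can look cleaner than the experience of the cohort. There is no concurrent control group, so the reading of safety also depends on defining events in the same way here and in the historical cohort.

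The surgery item raises a smaller question. It excludes only primary closure, while the section elsewhere speaks of final closure, which implies that closure can take more than one procedure. The abstract limits the measure to unexpected operations and the outcome list does not. Two sites abstracting records under an undefined term could treat a planned second-stage closure differently.

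**Working it through.** The plan gives no figure for any adverse event rate, so the main check is of the text. The article's only precision statement (Sample size) does reproduce. The worst-case half-width 1.96 × √(0.25/n) is 15.5 points at n = 40 (stated: less than 16) and 21.9 points at n = 20 (stated: less than 22). Neither figure depends on the two definitions.

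**1. Is the sign an artefact of text extraction?** Probably not. The greater-than-or-equal sign survives in Eligibility criteria (gestational and maternal age) and in Feasibility objective outcomes (the 80%, 85% and 90% targets).

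**2. Does another section correct the threshold?** No. NEC is not staged anywhere else, no staging system is named, and nothing says that Stage II is included.

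**3. What can the wording do to the reported rate?** Enrolment of 20 is from Sample size. The two cases are illustrative.
- Counting Stage II: 2/20 = 10%.
- Not counting it: 0/20. The exact two-sided 95% upper limit solves (1 − p)^20 = 0.025, so p = 1 − 0.025^(1/20) = 0.168.

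**4. Sensitivity to assumed rates.** The documents give no NEC rate by stage. Let r be the assumed rate of Stage II or higher and s the assumed share of those cases that are exactly Stage II. The expected count is 20r with Stage II included and 20r(1 − s) without it. The chance of at least one counted case is 1 − (1 − p)^20, with p = r or p = r(1 − s).

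| r | s | Expected, Stage II or higher | Expected, above Stage II | P(≥1), Stage II or higher | P(≥1), above Stage II |
|---|---|---|---|---|---|
| 2% | 30% | 0.4 | 0.28 | 0.33 | 0.25 |
| 2% | 70% | 0.4 | 0.12 | 0.33 | 0.11 |
| 5% | 50% | 1.0 | 0.5 | 0.64 | 0.40 |
| 10% | 30% | 2.0 | 1.4 | 0.88 | 0.77 |
| 10% | 70% | 2.0 | 0.6 | 0.88 | 0.46 |

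Across these ranges the sign alone can decide whether any NEC is reported.

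**5. The surgery wording, side by side.**
- Abstract: operations that are unexpected.
- Adverse event list: operations that are additional, with primary closure as the only exclusion.
- Feeding times, same section: measured from final closure.

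'Primary closure' could mean the initial repair however achieved, or a one-step repair as opposed to a staged one. The text does not settle which.

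**The case against.** **On NEC.** The threshold could be deliberate. The list of adverse events is introduced as open-ended, adverse events in general are captured from reports and records, and the principal investigators then grade them. The monitoring committee reviews study data, not only this rate. No stated stopping rule or numerical feasibility criterion uses it; the four criteria are enrolment, adherence, fidelity and withdrawal. All of this stands. It means that a Stage II case need not be lost to the trial, and that calling the cut-off an error goes further than the documents allow. It does not put the case into the rate that is named, reported and open to historical comparison.

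A reader might also infer that NEC is the only feeding-related harm on the list. The article does not say so, and it gives no ground for treating sepsis, compartment syndrome or re-operation as unrelated to feeding.

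**On surgery.** A reader might infer that every planned staged closure is counted as an adverse event. That follows only if primary closure means one-step closure and a planned final closure counts as additional. The word 'additional', the adverse event heading and the abstract's 'unexpected' all point the other way, and the feeding-pathway figures are not available to check. Nor does the text support saying that true re-operations would be hidden, because they are counted on either reading. What remains is an undefined term and a mismatch between sections.

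**Conclusion.** The NEC point holds as a matter of plain wording: Stage II is outside the named rate, and no other section corrects this. Whether that was intended cannot be known from the documents. The size is a matter of one or two cases among 20 infants, for example 0/20 with an upper limit of 16.8% against 2/20. The case counts and stage-specific rates behind these illustrations are assumptions. Since the change is nearly free and the outcome bears on the safety of early feeding, it should be made.

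The surgery point is minor and concerns consistency of wording only. No size is attached to it, because any figure would need both an assumed share of staged closures and a reading of primary closure that the text does not establish.

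**What to change.** 1. Define the outcome as NEC Stage II or higher and report it by stage, so that the count above Stage II stays visible. If the strict cut-off was intended, the stage breakdown still provides it.
2. Replace the surgery item with unplanned abdominal operations after final abdominal closure, whether the closure was primary or staged. This agrees with the abstract and with the closure time used for the feeding outcomes.
3. Apply both definitions to the historical cohort where its data allow, and state where they do not.

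The cost is two phrases in the outcome list. For enrolled infants the information should come from the record review already planned. Whether the historical database holds NEC stage and the timing and planning of operations is not shown and needs checking. The downside is a possibly higher NEC count than under the present wording.

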## Trial design

This study is a single-arm feasibility trial. All enrolled neonates will receive the intervention. This trial is not designed to test hypotheses regarding efficacy.

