#### Adverse event reporting and harms

Potential adverse events will be discussed and categorized (based on severity, expectedness and relatedness) by the principal investigators.

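### If adverse-event rates are compared with the historical cohort, unequal case-finding could create an apparent excess in the trial cohort, and adjusting for site cannot remove it

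*Protocol article*

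**What the plan says.** Four statements in the protocol article bear on this point.

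- **Finding events in the trial cohort** (Exploratory outcomes): "Medical errors and adverse events will be obtained via solicited reports and review of EHR data".
- **Events of interest** (same section): "Outcomes of adverse events include rates of necrotizing enterocolitis (> Stage II), sepsis, abdominal compartment syndrome, additional abdominal surgeries (excluding primary closure), and mortality".
- **Source of the comparison cohort** (same section, opening paragraph): "These measures will be compared to a historical cohort using the existing UCFC database".
- **Analysis** (Methods for additional analyses, including comparisons to historical controls): "For comparisons to historical controls on the study variables described earlier, we anticipate being able to obtain patient-level data from the historical controls". Linear and logistic regression then give adjusted mean differences or odds ratios "with 95% confidence intervals for the current vs. historical control comparisons, adjusting for study site". If only summary figures can be had, stratified means or proportions of the current cohort are set beside the historical ones.

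The article does not say how the database identified or defined adverse events. It describes no step that aligns event finding between the two cohorts.

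**The concern.** Events in the trial cohort have two routes into the data: staff are asked about them, and the record is reviewed. The historical data were already assembled, so the trial's own solicitation cannot be applied to them. An event that surfaces only because someone asked would count in the current cohort and might have no counterpart in the historical one.

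The method of case-finding would then coincide with the cohort indicator. The regression coefficient for current versus historical would absorb both any effect of early feeding and any difference in ascertainment, and the two could not be separated.

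Safety is named in the Objectives. With no concurrent control, the historical cohort is the only internal benchmark for event rates. A spurious excess could read as harm from early feeding or could hide a real reduction, in a study meant to inform later trials.

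**Working it through.** **The plan's own figures.** The article gives no figure for ascertainment. Its only design figures are the error margins under Sample size: below 16 and 22 percentage points for denominators of about 40 and 20. They reproduce as Wald half-widths at a proportion of 0.5:

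- n = 40: 1.96 × √(0.25/40) = 15.5 points
- n = 20: 1.96 × √(0.25/20) = 21.9 points

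The concern does not depend on them; they only give scale.

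**Inputs for the illustration.**

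- True sepsis rate p = 19% in both cohorts. This is the background figure in the Introduction (Gastroschisis: clinical significance), not a design input.
- Trial capture 100%: assumed.
- Database capture c relative to the trial: assumed, because the article gives none.

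**Formulae.** Observed historical rate h = c × p. With no true difference, the apparent odds ratio is [p/(1 − p)] ÷ [h/(1 − h)], where p/(1 − p) = 0.19/0.81 = 0.2346.

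| Database capture c (assumed) | h | h/(1 − h) | Spurious difference (points) | Spurious odds ratio |
|---|---|---|---|---|
| 100% | 19.0% | 0.2346 | 0 | 1.00 |
| 85% | 16.2% | 0.1926 | +2.9 | 1.22 |
| 70% | 13.3% | 0.1534 | +5.7 | 1.53 |
| 50% | 9.5% | 0.1050 | +9.5 | 2.23 |

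**Direction.** It reverses if the trial finds fewer events than the database. With trial capture 90% and database capture 100%, the observed rates are 17.1% and 19.0%, a difference of −1.9 points and an odds ratio of 0.88. Adding a second, active source makes this the less likely direction, but it is not excluded.

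**Why site adjustment does not help.** Suppose capture is c in the historical cohort at both sites and complete in the trial at both. With the same true rate at each site, the formula above applies within each site, so the site-adjusted odds ratio equals the crude one. The same section says that gestational age, birth weight, sex and race/ethnicity may also be accounted for if feasible. These do not measure how events were found either.

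**Scale against sampling error.** At 19% and n = 20, the expected count is 0.19 × 20 = 3.8 events. The 95% half-width is 1.96 × √(0.19 × 0.81/20) = 17.2 points. The illustrated shifts of 2.9 to 9.5 points correspond to about 0.6 to 1.9 events among 20 infants.

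**Which events are exposed.** Death and additional abdominal surgery leave a clear record in any source. Sepsis, the staging threshold for NEC and abdominal compartment syndrome depend more on definition and on how hard one looks. Medical errors are probably the item most dependent on being asked about, and no historical comparison of them is stated.

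**The case against.** **The comparison of safety rates is inferred.** No sentence says that adverse-event rates will be set against the historical cohort. The nine numbered exploratory endpoints contain no adverse event, and the abstract gives safety its own sentence, apart from the exploratory outcomes. This stands, so the point must be conditional. The section heading and the reference to study variables described earlier still make the comparison the natural reading, and nothing excludes it.

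**The database's methods are unknown.** It may itself rest on thorough chart review. This also stands. A reader might infer that the comparison is biased, but the documents support only a risk of bias.

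**The investigators' categorisation might be read as a further source of bias.** The section Adverse event reporting and harms says events are "categorized (based on severity, expectedness and relatedness) by the principal investigators". That concerns grading and attribution, not whether an event occurred. It does not support a difference in event rates, and the point does not rely on it.

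**The consequence is limited.** The four feasibility objectives use no historical safety contrast, and the article states: "This trial is not designed to test hypotheses regarding efficacy". At 20 infants, the illustrated shifts lie inside the sampling error. This limits the weight of the point but does not remove it: a confidence interval shows imprecision, whereas it does not show unequal ascertainment. The disclaimer also concerns efficacy, not safety.

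**An article condenses the full protocol.** Detailed event definitions and form design may fairly be left to documents not shown. The point does not rest on their absence. It rests on the article naming a two-source method for one cohort and a pre-existing source for the other under a heading that announces a comparison.

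**Conclusion.** The point holds as a conditional risk. If adverse-event rates are among the measures compared with the historical cohort, differential case-finding could produce an apparent excess in the trial cohort, and the stated adjustment for study site cannot correct it. The risk lies mainly with sepsis, NEC staging and abdominal compartment syndrome.

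Its size cannot be estimated from the documents. The odds ratios of 1.22 to 2.23 are illustrations. They rest on a background sepsis rate of 19% taken as equal in both cohorts, complete capture in the trial, and assumed database capture of 85% down to 50%. At equal capture there is no bias.

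The four feasibility objectives are unaffected. The change is still worth making, because it is cheap and without it the contrast would be hard to interpret.

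**What to change.** In Exploratory outcomes and in Methods for additional analyses:

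1. State whether adverse-event rates are part of the historical comparison. If they are not, one sentence saying so settles the matter.
2. If they are, state that the comparison counts, in both cohorts, only events identified from the source common to both (EHR or database abstraction) under one written definition per event. If only summary historical figures are available, count the trial events under the definition used for those figures.
3. Record for each trial event whether it was found by EHR or database abstraction, by solicited report, or by both.
4. Report solicited-only events and medical errors descriptively for the trial cohort, with no historical contrast.

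The cost is about two sentences of analysis text and one source field on the adverse-event form. Recruitment began in February 2025, so the field should be added soon and completed for infants already enrolled. The downside is that the compared rates omit solicited-only events, which remain visible in the trial cohort's own safety report.
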